### Data collection procedures

This is a community-based study, and data collection will be done at the community centers of each community. Data collection is expected to last for five months and the data collection sites for this study include community centers, households, churches and mosques. This will be done after permission is obtained from the gatekeepers in the community for community entry. The gatekeepers include, but not limited to traditional chiefs, opinion leaders, imams, pastors and assembly members. After satisfying all the requirements, ethical clearance for this study has been obtained from the University of Cape Coast (UCC) Institutional Review Board (IRB) with the number UCCIRB/EXT/2022/27. Data will be collected from two or more participants in a single household. For fair representation, participants aged ≥ 25 years will be randomly selected from each household. The purpose of the study, including the benefits and the risks involved will be clearly explained to the participants. After which verbal and written consent will be sought from the prospective participants who have agreed to participate in the study. Written and verbal informed consent will be obtained from each participant for each part of the study, including the survey questionnaires, anthropometric measurements, eye examination and biochemical sample collection.

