### Participants

Following the protocol of the Research on Obesity and Diabetes among African Migrants (RODAM) study, which focused on obesity and type 2 diabetes among African migrants (44), this study estimates the prevalence of undiagnosed type 2 diabetes (T2D) in the Cape Coast metropolis of Ghana, at 6-7%, and the prevalence of obesity at 17%. The study aims for a power of 0.90 with α=0.05, including the Bonferroni correction. Using these parameters, a sample size of approximately 1000 would be sufficient to detect a 10% proportion of undiagnosed T2D. In order to compensate for attrition, the study seeks to recruit 1200 self-identified healthy individuals from 13 urban and rural communities in the Cape Coast Metropolis, who have not been previously diagnosed of diabetes or prediabetes prior to the study for collection of baseline data.

Due to the large and geographically dispersed population, a multistage sampling technique would be employed to sample participants for this study. This will be done in three stages, where the first stage involves dividing the population into clusters, based on the already existing communities within the metropolis. The second stage involves sampling these clusters to be used in the study by using systematic random sampling. At this stage, 13 clusters representing 13 rural, peri-urban and urban communities would be selected for the subsequent sampling stage. Finally, the third stage would involve further sampling within each selected cluster to randomly select households, and recruit the first two persons from each family line (with random replacement) in the indigenous communities, while using convenience sampling in non-indigenous communities. It is envisaged that approximately 90-100 participants will be randomly selected from three rural communities (Efutu Mampong, and Efutu), four fishing communities (Abekam, Duakor, Ekon, and Ntsen), three peri-urban communities (Ayeko-Ayeko, Ankaful and Nkanfoa) and one urban community (UCC), two market communities (Kotokuraba and Abura Markets), and one artisanal community (Siwdu). Household mapping will be done utilizing the 2021 Housing Census Data. All the 1200 volunteers will be recruited from their communities of origin before disclosing any monetary benefits.

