### Questionnaire/survey questionnaire

The data collection consists of a survey questionnaire, anthropometric measurements, eye examination and collection of biochemical samples. The study will recruit volunteers from communities, markets, churches and schools in the 13 communities in rural, peri-urban and urban Cape Coast.

The WHO-STEPwise approach for identifying and explaining the risk factors for cardiometabolic diseases will be adapted in the data collection process of the CarMeR study. The WHO STEPwise questionnaire is adapted and modified to fit the Ghanaian NCDs context based on previous studies on NCDs in Ghana (45, 46). The first step involves gathering demographic and behavioral risk factor data using a questionnaire; the second step involves the collection of physical measurements; and the third step involves the collection of fasting blood samples for biochemical tests. In addition, the study will collect data on visual outcomes, including retinal changes, visual acuity, contrast sensitivity and visual field. The survey questionnaire consists of seven validated questionnaires that have been adapted to suit Ghanaian culture and the typical Ghanaian lifestyle. The survey questionnaire includes:

Perceived Stress Scale (PSS) (47): This questionnaire measures stress levels of participants in the past 1 month.Pittsburgh Sleep Quality Index (PSQI) (48): This questionnaire assesses sleep habits and quality of participants in the past 1 month.International Physical Activity Questionnaire (IPAQ) (49) assesses weekly physical activity levels of the participants.WHO STEPwise Inventory (40): This questionnaire assesses fruits and vegetable intake, smoking and alcohol consumption.Stunkard Figure Rating Scale (50): The Stunkard Figure Rating Scale assesses levels of body type satisfaction using a range of visual representations, starting from very slim (silhouette 1) to the point of significant obesity (silhouette 9).Visual Disability Questionnaire (51): This questionnaire assesses and quantifies the effects of visual impairment on daily activities.A validated questionnaire measuring neighborhood and environmental characteristics.

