### Enrollment visit

Prior to data collection, recruitment of participants is done by the research assistants (RAs). This is achieved through community engagement via the identified gatekeepers of the specific community. The gatekeepers subsequently organize their community members to engage with the research team. The RAs recruit eligible participants based on the inclusion criteria. The selected participants are assigned codes to anonymize them, and their contacts are collected. Participants who meet the inclusion criteria and agree to participate in the study are asked to sign an informed consent form. Prior to the day of the data collection, participants are called on phone and are reminded of the requirement to fast (8-12 hours), and not ingest any other fluid apart from water. Participants arrive at the study site at 6:30am as communicated to them, and they are asked to rest for a while before their vital signs were measured. Anthropometric measurements are taken, followed by baseline blood samples for FBG, creatinine, liver function tests (AST and ALT), and lipid profiles. After which, a three-point OGTT is performed to assess glucose tolerance. The whole and plasma blood samples are then sent to the CERL at University of Cape Coast, Ghana for analysis and preservation in a cryogenic freezer -40°C. The entire duration of the process is expected to last four hours. Subsequently, participants newly diagnosed with diabetes using a 2-hour glucose level between 11.1-17.0mmol/L (200-299mg/dL) are put into one cohort to complete 12 months lifestyle intervention program and monthly follow-ups. While participants identified with 2-hour glucose ≥ 17.0mmol/L (≥300mg/dL) are referred for medical treatment.

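### Adults within a household are taken as the first two persons in one section and drawn at random, in no fixed number, in another, so the within-household selection probability is undefined where households are sampled

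*Protocol article*

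**What the plan says.** The Participants section describes a multistage sample. Communities are chosen first, and the last stage is "further sampling within each selected cluster to randomly select households". Within that stage the plan is to "recruit the first two persons from each family line (with random replacement) in the indigenous communities, while using convenience sampling in non-indigenous communities". The same section then states that "approximately 90-100 participants will be randomly selected from three rural communities", in a sentence that runs on through the fishing, peri-urban, urban, market and artisanal communities without setting apart those sampled by convenience.

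Data collection procedures gives a different account. It says "Data will be collected from two or more participants in a single household", and in the next sentence, with fair representation as the reason, that "participants aged ≥ 25 years will be randomly selected from each household".

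Two further sections describe how people reach the study. Under Questionnaire/survey questionnaire: "The study will recruit volunteers from communities, markets, churches and schools in the 13 communities". Under Enrollment visit: "The gatekeepers subsequently organize their community members to engage with the research team".

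The Exclusion criteria section names the prevalence of undiagnosed diabetes as the primary objective. Data analysis plans to report it as percentages with confidence intervals.

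**The concern.** Taking the first two people is not a random draw, because the outcome depends on whatever determines who comes first. A field team working from the Participants section and one working from Data collection procedures would enrol different people from the same house.

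A population prevalence needs to know how likely each person was to be included. If those who come first differ from the rest of the household in age, occupation or health, the estimate is off by an amount that a larger sample does not reduce and the confidence interval does not show. This cannot be repaired at analysis: if selection was not random, or the number eligible was not recorded, the probability cannot be recovered afterwards.

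**Working it through.** No stated figure has to be reproduced. The check is a comparison of the two sections, followed by what each rule implies for the selection probability.

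**1. The two rules side by side**

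| | Participants | Data collection procedures |
|---|---|---|
| Method | the first two, order not defined | random draw |
| Number | two | two or more, no ceiling |
| Unit | family line | household |
| Where | indigenous communities only; convenience sampling elsewhere | each household, no restriction |

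The remark about random replacement in the Participants section does not say that the initial two are drawn at random. The real conflict is in the method. The count and the unit also differ.

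**2. Selection probability under each rule**

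If k adults are drawn at random from H eligible adults, each has probability k/H and weight H/k.

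- Random draw of exactly two: H = 2, 3, 4, 6 gives 2/2 = 1.00, 2/3 = 0.67, 2/4 = 0.50, 2/6 = 0.33, with weights 1, 1.5, 2, 3. All are known once H is recorded.
- Two or more, number left open: for H = 6, k = 2, 3 or 4 gives 0.33, 0.50 or 0.67. The design does not fix the value.
- First two: no probability can be assigned, because the order is undefined.

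The spread from 1 to 0.33 does not measure harm from the contradiction. It would occur under the correct rule too, and shows why H must be recorded.

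**3. Possible effect on prevalence (hypothetical in size and direction)**

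Take a true prevalence of 6.5%, the middle of the 6-7% in the Participants section. Everything else here is assumed: half of adults are readily reached, they form a share w of the sample, and their prevalence is r times that of the rest. Then the prevalence in the rest is b = 6.5/(0.5r + 0.5), and the estimate is w·r·b + (1 - w)·b.

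- r = 1.25, w = 0.6: b = 5.78, r·b = 7.22; estimate 0.6 × 7.22 + 0.4 × 5.78 = 6.6%, a bias of +0.1 points.
- r = 2, w = 0.9: b = 4.33, r·b = 8.67; estimate 0.9 × 8.67 + 0.1 × 4.33 = 8.2%, a bias of +1.7 points.
- If those readily reached have the lower prevalence, the two values swap and the bias runs from -0.1 to -1.7 points.

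For scale, the simple-random-sample 95% half-width at n = 1000 is 1.96 × √(0.065 × 0.935/1000) = 1.5 points. The illustration treats the whole sample as recruited this way. The first-two rule covers only indigenous communities, so its effect on a pooled estimate would be smaller.

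**4. Clustering**

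With m people per household and an assumed within-household correlation of 0.05-0.2, the design effect 1 + (m - 1) × correlation is 1.05-1.2 for m = 2 and 1.1-1.4 for m = 3. This arises under any rule that takes more than one person, including the one proposed below. It is a reason to fix the number and record the household.

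**The case against.** Several stronger readings are tempting, and the documents do not support them.

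- *Three mutually conflicting rules.* Two or more is a count, and it is compatible with a random draw. It could even fit two per family line if a household holds more than one line. What conflicts in method is one pair of statements.
- *The first-two rule governs the whole study.* It is confined to indigenous communities.
- *The household rules are why selection probabilities are unknown, and a household rule would make them known.* Convenience sampling, recruitment of volunteers and gatherings organized by gatekeepers leave probabilities unknown in part of the sample whatever is done within households.
- *Prevalence will be overestimated by a stated amount, because people at home are sicker.* The text does not say that first means first found at home. The share readily reached and the difference in prevalence are nowhere given, and the sign can go either way.

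It can also be said that weights, clustering adjustment, listing forms and call-back limits belong in an analysis plan or field manual. That is fair, and their absence is not the point. What remains is that the article states two selection rules that cannot both be followed, and an analysis plan cannot supply a selection probability that the fieldwork did not create.

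**Conclusion.** The point holds in a limited form. In the communities where households are sampled, the sections disagree on whether adults are taken in order or drawn at random, and they leave the number open. The within-household selection probability is therefore undefined, and the primary prevalence estimate is exposed to selection bias. This conclusion rests on the text alone and on no assumed value.

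The size and direction of the bias cannot be determined from the documents. The range of 0.1 to 1.7 points either way depends wholly on invented inputs and should not be cited as an expected error. The matter should be settled before enrolment, since it affects the main result, is easily corrected at that stage and is hard to repair later.

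**What to change.** State one rule in both Participants and Data collection procedures. In each sampled household, list the eligible adults aged 25-70, draw a fixed number at random (two, or all if fewer), and record the number eligible. If family line is to remain a unit, say how it relates to the household. Weight prevalence by eligible/selected at this stage, and carry the household as a cluster in the confidence interval.

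Name the communities recruited by convenience, volunteering or gatekeepers. State that they are non-probability samples to which these weights do not apply, report them as such, and change the sentence that describes random selection in every listed community.

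The cost is some listing time. Household mapping from census data is already planned, tablets are in use, and recruitment comes before data collection, so the list and the draw fit the existing workflow. A call-back scheme would be useful but is optional and less clearly cheap: at the stated maximum of ten participants a day, 1200 people need 1200/10 = 120 field days, while five months hold about 5 × 52/12 × 5 = 108 weekdays.

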### Questionnaire/survey questionnaire

The data collection consists of a survey questionnaire, anthropometric measurements, eye examination and collection of biochemical samples. The study will recruit volunteers from communities, markets, churches and schools in the 13 communities in rural, peri-urban and urban Cape Coast.

The WHO-STEPwise approach for identifying and explaining the risk factors for cardiometabolic diseases will be adapted in the data collection process of the CarMeR study. The WHO STEPwise questionnaire is adapted and modified to fit the Ghanaian NCDs context based on previous studies on NCDs in Ghana (45, 46). The first step involves gathering demographic and behavioral risk factor data using a questionnaire; the second step involves the collection of physical measurements; and the third step involves the collection of fasting blood samples for biochemical tests. In addition, the study will collect data on visual outcomes, including retinal changes, visual acuity, contrast sensitivity and visual field. The survey questionnaire consists of seven validated questionnaires that have been adapted to suit Ghanaian culture and the typical Ghanaian lifestyle. The survey questionnaire includes:

Perceived Stress Scale (PSS) (47): This questionnaire measures stress levels of participants in the past 1 month.Pittsburgh Sleep Quality Index (PSQI) (48): This questionnaire assesses sleep habits and quality of participants in the past 1 month.International Physical Activity Questionnaire (IPAQ) (49) assesses weekly physical activity levels of the participants.WHO STEPwise Inventory (40): This questionnaire assesses fruits and vegetable intake, smoking and alcohol consumption.Stunkard Figure Rating Scale (50): The Stunkard Figure Rating Scale assesses levels of body type satisfaction using a range of visual representations, starting from very slim (silhouette 1) to the point of significant obesity (silhouette 9).Visual Disability Questionnaire (51): This questionnaire assesses and quantifies the effects of visual impairment on daily activities.A validated questionnaire measuring neighborhood and environmental characteristics.

In addition to these standard questions, data will also be collected on the sociocultural background, demographics, early life experiences, behavioral patterns (hydration habits and substance consumption) environmental exposures, and family history of disease (diabetes, hypertension, diabetes, cancer, asthma). The survey questionnaire is administered by a team of four trained enumerators, and a supervisor who is a senior fellow and cardiometabolic disease researcher with expertise in field surveys. Participants who have consented to participating in the study will be scheduled for a systematic interview. A maximum of ten participants will be engaged each day and the interviews will be conducted right after the first blood sample is collected. The interviews will conducted face-to-face by enumerators with participants in their preferred Ghanaian languages, including Fante, Twi, Ewe, and as well as English for those who are literate and proficient in the English language. The interview for each participant is expected to last approximately 30-45minutes. The interview will be conducted using the Samsung Galaxy Tab E and the data collected from participants will be transmitted to an online server that is managed through the Kobo Collect toolbox application (https://www.kobotoolbox.org). Using the Kobo Collect toolbox, the completeness and quality of the data input are cross-checked by the research assistants and the principal investigator at regular intervals (52, 53).

### Anthropometric measurements

Physical body measurements will be performed using standard equipment validated by international bodies for such protocols. Anthropometric measurements of height, weight, waist circumference, waist-to-hip ratio, and bioimpedance analysis will be performed using the GS6.5B Body Composition Analyzer. Bioimpedance analysis involves the assessment of total body fat, metabolic age, and muscle mass. The device uses these impedance values to calculate various body parameters such as body fat percentage, BMI, muscle mass, hydration status, basal metabolic rate, and metabolic age. Once these measurements are complete, the bioimpedance device displays the results on the screen and produces a printout of the results. Vital blood pressure statistics, including systolic BP, diastolic BP, and pulse rate are measured three times for each participant using the Sinocare BSX 516 Arm-Type Electronic Blood Pressure Monitor. The values of the three measurements are collated and the average is computed.

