Due to the demographic characteristics and nature of diabetes, the biopsychosocial model of disease development underpins the CarMeR Study. The model as utilized in a previous study, propounds that disease occurrence results from the interplay of biological, psychological and social factors (37). It explains how factors, including biological factors (family history diabetes, sex), sociological factors (familial, occupation, economic status, nutrition, ethnicity, place of birth and early life experiences), and psychological factors (stress and sleep patterns) contribute to disease development. The biopsychosocial model suggests that each of these three domains has an influence on health. The biopsychosocial model has been selected because it provides a framework for understanding risk factors associated with CMDs in Ghana. As illustrated in **Figure 1**, we hypothesize that genetic factors, social factors, familial factors, stress, economic status, religion, ethnicity, nutrition patterns, physical activity and other population characteristics play a crucial role in determining an individual’s susceptibility to CMDs. Incorporating these factors into our conceptual model, we envisage gaining a deeper understanding of the complex interactions that contribute to the risks of CMDs such as diabetes, obesity, hypertension, and other cardiovascular diseases. This model will explore the prevalence of undiagnosed diabetes, prediabetes and hypertension among critical populations in Ghana, and how various factors predispose individuals to risk of cardiometabolic diseases.

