## Methods

The CarMeR Study will be executed by a multidisciplinary team of researchers from the University of Cape Coast, its Directorate of Health Services, the Rwanda National Hospital, and the University of Global Health Equity, Rwanda. To obtain reliable and valid results, the CarMeR Study will adhere to gold standards in all aspects of the project, including but not limited to the selection of communities, standardization of study protocols, adherence to ethical principles in the sampling procedures, anthropometric measurements, blood glucose testing, chemistry measurements, eye examination, blood pressure measurements, and surveys. The CarMeR Study will adopt the WHO-STEPwise approach for assessing cardiometabolic risk factors The STEPwise approach to surveillance (STEPS) is an NCD surveillance tool recommended by the WHO since 2005 for monitoring trends across countries (38, 39). The WHO-STEPwise instrument comprises three distinct phases or “steps” for evaluating risk factors. The first step is a questionnaire-based assessment, the second step comprises of physical measures and the third step comprises of biochemical measures (40). This instrument is a simplified and standardized approach to surveillance for collecting, analyzing and disseminating data on key risk factors especially for NCDs (38). In addition to a questionnaire survey, a community-based quasi-experimental design will be utilized to assess the glucose tolerance of all participants after administration of 82.5g monohydrate dextrose, in order to ascertain the prevalence and risk factors for undiagnosed diabetes and prediabetes. Subsequently, all consenting participants diagnosed with abnormal glucose tolerance will be enrolled into a community-based randomized controlled trial (RCT) to measure the effectiveness of lifestyle interventions on diabetes remission.

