### Data analysis

For the accuracy of data and information, data collected through the Kobo Collect toolbox application will be downloaded into an Excel spreadsheet and screened visually and statistically. Data will be analyzed and interpreted by the principal investigator and his local collaborators and shared back with foreign collaborators. In the attempt to make the findings of the study public, data analysis will be conducted using STATA 16 and SPSS 23. Statistical tools specific and relevant to the research questions and hypotheses of the CarMeR study would be used. To determine the prevalence of undiagnosed diabetes, prediabetes and other associated cardiovascular risks, data on OGTT, FPG and HbA1c will be analyzed using descriptive statistics (percentages and confidence intervals). In order to investigate the differences in phenotype, diabetes, prediabetes, and normoglycemic groups will be compared based on BMI and body composition (waist hip ratio, body fat percentage, skeletal muscle, total body water) using analysis of variance (ANOVA) and t-test. To profile the ocular characteristics and complications of the diabetes and prediabetes groups, a cross-tabulation and a subsequent chi-square test will be done to assess the association between glycemic dysregulation and the presence of ocular complications (diabetic retinopathy, cataract, macular edema). For the purpose of ascertaining whether the predominant etiological factor of undiagnosed diabetes in this populations is insulin resistance or beta-cell failure, a homeostasis model analysis of beta [HOMA-β and HOMA-IR] will be computed and logistic regression will be used to determine the dominant factor. As a way of determining the sensitivity of other diagnostic alternatives (FPG and HbA1c) in comparison to the multi-sampled OGTT, receiver-operated characteristics (ROC curves), including sensitivity and specificity curves, will be used. Finally, to ascertain whether lifestyle changes (food choice, physical activity, weight loss, psychosocial counseling) over a one-year period impacts biomarkers of glucose regulation, a linear mixed model regression analysis, controlled for baseline characteristics will be used. T-tests will be conducted to observe changes in glucose regulation biomarkers.

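### Blood pressure is averaged over all three readings including the first; if the first runs high, hypertension prevalence is pushed up, and using the second and third readings would avoid this at almost no cost.

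*Protocol article*

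**What the plan says.** Under Anthropometric measurements, systolic pressure, diastolic pressure and pulse "are measured three times for each participant using the Sinocare BSX 516 Arm-Type Electronic Blood Pressure Monitor". The next sentence gives the combining rule: "The values of the three measurements are collated and the average is computed". No reading is said to be dropped.

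Under Enrollment visit, participants arrive at 6:30am after fasting and "they are asked to rest for a while before their vital signs were measured". The length of the rest is not given. Anthropometry and blood sampling follow.

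Hypertension is among the conditions whose prevalence is of interest. The Introduction says: "This model will explore the prevalence of undiagnosed diabetes, prediabetes and hypertension among critical populations in Ghana". It also lists hypertension with obesity and diabetes as a cardiometabolic risk factor, and objective 1 covers associated cardiovascular risks. Data analysis reports prevalence as percentages with confidence intervals. The Diagnoses section defines diabetes, prediabetes and obesity but gives no blood pressure cut-off.

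**The concern.** The averaging rule is stated, so this is not a gap that a fuller document would be expected to fill. Prevalence of a condition defined by a cut-off depends on how many people lie just below it, so a small systematic shift in the measured value moves a noticeable number across.

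If the first of three same-visit readings tends to be higher than the later ones, averaging it in shifts everyone's value upward. That error has one direction and does not shrink as more people are recruited, whereas the confidence interval does. The reported interval would then be centred too high, and some people near the cut-off would be classed as hypertensive only because of the first reading. The two readings needed to avoid this are already planned.

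**Working it through.** **Inputs from the protocol article**
- Three readings, all averaged (Anthropometric measurements).
- Sample: "the study seeks to recruit 1200 self-identified healthy individuals from 13 urban and rural communities" (Participants), so n = 1200.
- Multistage sampling over 13 clusters; no design effect given (Participants).

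**Inputs that are assumptions**
- d, the excess of the first reading over the mean of the second and third: 0 to 8 mmHg.
- Systolic SD 20 mmHg (range 18 to 22), normal distribution.
- Hypertension prevalence based on readings two and three: 30% (range 20 to 40%).
- Design effect 1, with 2 as an illustration of clustering.

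**The plan's own figure.** The article states no figure for blood pressure. Its only related figure is the sample size: "a sample size of approximately 1000 would be sufficient to detect a 10% proportion of undiagnosed T2D". With p0 = 0.07 (upper end of the stated 6–7%), p1 = 0.10, power 0.90 and a two-sided alpha of 0.05/2 (two comparisons assumed, since the number is not given):

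n = [2.241 × √(0.07 × 0.93) + 1.282 × √(0.10 × 0.90)]² / 0.03² ≈ 1017.

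This agrees with about 1000, but only under that assumed correction. Recruiting 1200 allows for losing one in six: 1000 / (1 − 1/6) = 1200. The calculation concerns diabetes; here it only supplies n.

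**Step 1: shift in the mean.** Let m be the mean of readings two and three. The three-reading mean is (m + d + 2m)/3 = m + d/3.

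**Step 2: shift in prevalence.** Bias = 1 − Φ(z − d/(3 × SD)) − p, where z is the normal quantile at 1 − p. For p = 0.30, z = 0.524. Example, d = 5, SD = 20: 1 − Φ(0.524 − 5/60) = 1 − Φ(0.441) = 0.330, a bias of 3.0 points. Near d = 0 the slope is 0.348/60 = 0.0058, or about 0.6 points per mmHg of d.

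**Step 3: comparison with sampling error.** Half-width = 1.96 × √(0.30 × 0.70 / 1200) = 2.6 points. With a design effect of 2 it is 2.59 × √2 = 3.7 points.

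| d (mmHg) | Shift in mean (mmHg) | Bias (points) | People of 1200 | Ratio to half-width | Ratio, design effect 2 |
|---|---|---|---|---|---|
| 0 | 0 | 0 | 0 | 0 | 0 |
| 1 | 0.33 | 0.6 | 7 | 0.22 | 0.16 |
| 3 | 1.00 | 1.8 | 21 | 0.68 | 0.48 |
| 5 | 1.67 | 3.0 | 36 | 1.14 | 0.81 |
| 8 | 2.67 | 4.8 | 57 | 1.85 | 1.31 |

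**Step 4: sensitivity to SD and prevalence.** Over SD 18–22 and prevalence 20–40%, d = 3 gives 1.3–2.2 points and d = 5 gives 2.2–3.6. The bias equals the simple-random-sampling half-width (2.3–2.8 points) at d of about 3.8–5.2 mmHg. It equals the full interval width only at about 7.6–10.0 mmHg.

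**Step 5: price of using two readings.** With an assumed between-person SD of 18 and a within-visit SD w of 5 or 7 mmHg, the SD of the analysis value goes from √(18² + w²/3) = 18.2 or 18.4 to √(18² + w²/2) = 18.3 or 18.7. With an assumed mean of 126 and cut-off of 140, the extra spread by itself raises prevalence by about 0.1 to 0.3 points, a small offset to the correction.

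**The case against.** The strongest reply is that nothing in the article says the first reading is higher, or by how much. If d is zero there is no bias, and averaging three readings is a clear and consistent rule. This stands, and it is why the point has to be conditional.

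Several further replies also stand:
- The link to a cut-off is inferred. The article gives no hypertension definition, and its prevalence sentence in Data analysis names only the glucose tests and HbA1c. If the definition also counted people with known or treated hypertension, the shift would be diluted.
- The rest before measurement may reduce any first-reading effect. Its unstated length is the kind of detail an article leaves out and is no fault.
- A reader might take the Discussion's remarks on blood-draw discomfort as evidence of a raised first reading. They concern people declining to continue. Worry about coming blood draws could raise all three readings equally, and dropping the first would not help.
- The study says "The CarMeR Study will adopt the WHO-STEPwise approach for assessing cardiometabolic risk factors", but the article does not reproduce that method's rule for combining readings, so no departure from it can be claimed.
- A reader might also infer that the bias is as large as the confidence interval. The documents cannot support that: it matches only the half-width, only at d of about 4–5 mmHg, and only if clustering is ignored.

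None of this favours keeping the first reading in the main value. If d is zero, leaving it out costs very little; if d is positive, leaving it out removes a one-directional error.

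**Conclusion.** The point holds in conditional form. The analysis value includes the first reading; if that reading is systematically high by d, mean pressure is overstated by d/3 and hypertension prevalence by about 0.6 points per mmHg of d. The d/3 shift is exact. The prevalence figure rests on an assumed normal distribution, SD 20 mmHg and prevalence 30%, and on hypertension being counted from this mean against a cut-off. The plausible effect runs from nothing to somewhat more than the half-width of the interval, depending on a quantity that only the study's own readings can show.

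Priority is low. The Exclusion criteria section gives the prevalence of undiagnosed diabetes as the primary objective; hypertension is a secondary descriptive result. The documents neither contradict themselves nor miscalculate here.

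**What to change.** In Anthropometric measurements, keep the three readings and amend the combining rule to say that:
- each of the three readings is recorded and retained individually;
- the value used for hypertension prevalence and other blood pressure analyses is the mean of the second and third readings;
- the three-reading mean is reported as a sensitivity result, together with the observed mean difference between the first reading and the mean of the other two.

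The last item replaces the assumed d with the study's own figure. The change concerns analysis only and alters no clinical rule. It costs a short edit, with no new data, staff or visits. The downside is a very small loss of precision (SD from about 18.2–18.4 to 18.3–18.7 mmHg under the assumptions above) and a possibly lower hypertension figure.
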